### Cost-effectiveness of dual active ingredient insecticide-treated bed nets

There are two sources of incidence data that could be combined into the cost-effectiveness analysis. First, incidence rate ratios calculated from routine health management information system data can be used to provide summaries for each setting, allowing for the exploration of the range of cost-effectiveness potentially offered by the dual-AI ITNs. Second, individual-based stochastic models that capture the mechanisms of malaria transmission [47, 49] can be parameterized with the pilot study data including estimates for insecticide resistance (approximated as the proportion of mosquitoes surviving exposure to the discriminatory dose of pyrethroid at bioassay testing), treatment-seeking behaviour, timing of intervention deployment and subsequent adherence to net use by communities, mosquito species and related bionomics. The entomological efficacy of IG2, PBO, and standard pyrethroid-only ITNs have been separately determined using systematic review of experimental hut data [43, 52] (with that for RG ITNs to follow using additional bioassays and experimental huts allowing the inclusion of the impact of pyriproxyfen on oviposition and adult emergence rates [53]). These inform the transmission model to allow predictions to be made about epidemiological efficacy as resistance, approximated using the percentage survival of mosquitoes testing in the discriminatory bioassay, changes. The process is broadly able to predict pyrethroid- and PBO ITNs for the recent Tanzania trail [10, 44], and ongoing work will determine the validity of the framework systematically across multiple RCTs. Sensitivity analyses covering the range of parameter estimates observed during cross-sectional surveys can be performed for each cohort included in the pilot study using the transmission model framework. These models then provide a mechanism to predict the potential effectiveness in terms of cases averted or lives saved across other ecological settings.

The costs of each net distribution will be measured from a provider perspective and financial and economic costs calculated using an ingredients-based approach. Financial costs reflect the explicit expenditure of money associated with a programme, and economic costs reflect total resource use, or opportunity costs of a project, some of which may not be explicitly accounted for in a record of programme expenditures (such as volunteered time). The ingredients approach, or micro-costing, entails identifying all inputs to a process and assigning unit cost to each input. Costs are collected retrospectively for all campaign activities, including pre-distribution planning; household registration and community sensitization; net transportation and storage; distribution of nets to recipients; social and behaviour change communication; and monitoring and evaluation from financial and operational records, reports, pay scales, budgets, and invoices, as well as operational protocols and reports. Stakeholder interviews or resource-use survey instruments may be utilized to capture costs or resource inputs not reflected in financial or other records, such as volunteer time or assets used during the distribution but owned prior to the distribution (i.e., company vehicles), and national, regional, and local-level supervision time, or shared resources that are not included in standard financial reports. Additionally, primary cost data collection will be supplemented by a systematic review of published literature to ascertain uncertainty around measured cost estimates especially for use in probabilistic sensitivity analyses.

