**Methods:**

Observational pilot studies are ongoing in Burkina Faso, Mozambique, Nigeria, and Rwanda, leveraging dual-AI ITN rollouts nested within the 2019 and 2020 mass distribution campaigns in each country. Enhanced surveillance occurring in select study districts include annual cross-sectional surveys during peak transmission seasons, monthly entomological surveillance, passive case detection using routine health facility surveillance systems, and studies on human behaviour and ITN use patterns. Data will compare changes in malaria transmission and disease burden in districts receiving dual-AI ITNs to similar districts receiving standard pyrethroid-only ITNs over three years. The costs of net distribution will be calculated using the provider perspective including financial and economic costs, and a cost-effectiveness analysis will assess incremental cost-effectiveness ratios for Interceptor® G2, Royal Guard®, and piperonyl butoxide ITNs in comparison to standard pyrethroid-only ITNs, based on incidence rate ratios calculated from routine data.

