## Study objectives

The overall aim of the study is to describe the effectiveness and cost-effectiveness of IG2, RG, and PBO ITNs in comparison to standard pyrethroid-only ITNs. Specific objectives are organized into five study components: (1) malaria epidemiological surveillance to evaluate the impact of dual-AI ITNson malaria burden, (2) entomological surveillance to evaluate the impact of dual-AI ITNs on key entomological outcomes (3) anthropological data to assess how transmission risk is influenced by human behaviours, (4) assessment of the chemical and physical durability of the new ITN types, and (5) evaluation of the cost and cost-effectiveness of dual-AI ITNs.The epidemiological objective is to evaluate the effectiveness of IG2, RG, and PBO ITN distributions, compared to standard pyrethroid-only ITN mass distributions, in reducing:Malaria prevalence measured during annual cross-sectional surveys in children 6 months to 5 years (Burkina Faso, Mozambique, and Nigeria) and all ages (Rwanda).Passive malaria case incidence rates measured using routine surveillance systems (DHIS2).The entomological objective is to compare post-ITN distribution trends in vector densities, human biting rates, and entomological inoculation rates using CDCLTs and HLCs and to establish baseline. In addition, entomological objective is to evaluate insecticide susceptibility patterns in the primary vector species populations.The anthropological objective is to assess how human behaviour influences exposure risk and understand the key drivers of ITN use and non-use behaviour across districts with different types of ITN types.The ITN durability monitoring objective is to assess the attrition, survivorship, physical integrity, and insecticidal bioefficacy of all ITN types at baseline, 12 months, and 24 months.The cost-effectiveness objective is to combine data on product effectiveness (based upon case incidence rates measured for objective 1) and data on product prices and costs of delivery and deployment to estimate a mean cost per case averted for each ITN type.

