For passive case detection (PCD), an observational time-series study design using malaria surveillance data from the district health system will be used to compare trends in malaria case incidence in all age groups using a difference in differences approach. Monthly crude case incidence rates will be calculated at the health facility level by dividing the number of all positive malaria tests (RDT and blood smear) obtained that month by the estimate health facility catchment area population. Appropriate multivariate regression models accounting for the clustering of health facilities by district and for possible confounding factors (e.g., a negative binomial regression analysis of monthly case incidence rates likely to include rainfall amount and health facility catchment area population size), will also be utilized to estimate incidence rate ratios and incremental protective efficacy for IG2, PBO and RG ITNs. Alternatively, test positivity rates (the number of negative and positive test results obtained from suspected cases at the health facility level, stratified by study arm) may also be used to obtain odds ratio estimates from an appropriate logistic regression model. Raw datasets will be cleaned and transformed using Microsoft Excel (Microsoft Corp., Redmond WA) and Tableau v10 (Tableau Software Inc., Seattle WA) and all formal statistical analyses will be done using Stata v14 (StataCorp LLC, College Station TX).

ITN ownership, use, and coverage estimates will be calculated using standard methods recommended by the Surveillance, Monitoring and Evaluation Working Group of the RBM Partnership to end Malaria (https://endmalaria.org/node/990/related-material).

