#### Costing and cost-effectiveness data analysis

The time horizon for cost analysis fits the duration of study, respective to setting. Costs are presented as a table of inputs, unit prices, quantities, and line item and activity codes, as possible. Costs are divided into capital and recurrent costs, based on the lifetime of the goods or service being purchased. Capital costs are discounted in the economic analysis using lifetimes determined through stakeholder interviews, expert information, and prior published literature and a discount rate of 3% (in base case scenario analysis). Varying discount rates and lifetimes are examined in sensitivity analyses. Both financial and economic analyses will be conducted. These two types of analysis show (1) financial costs (what the explicit expenses of running a programme are) and (2) economic costs (the value of all resources used during study duration). In the financial analysis, capital costs are not discounted and are applied in full at the time of purchase. All costs must be converted to a common year and currency, to ensure comparability between settings with different inflation rates and currency values. Costs are converted from local currency to US dollars using the exchange rate for the year the cost analyses are conducted. The Consumer Price Index adjustment is used to inflate or deflate all costs. Next, costs are split into two categories: tradable costs (e.g., nets) and non-tradable costs (e.g., personnel, training, supervision, social and behaviour change communication). Non-tradable costs are further converted to 2020 international dollars. This is accomplished using the purchasing power parity ratios for the countries in which the costs were incurred. For comparability and interpretability across settings, results for all countries will be presented in both 2020 US dollars and international dollars.

Costs are reported in three ways: total economic cost of the programme, total cost by activity and line item, and the total cost per output. Total cost is simply total economic cost of the mass distribution of long-lasting insecticide-treated nets over their expected lifetime. The total cost is then broken down by activity and line item. Finally, the total cost is reported as a ratio over selected outputs, such as nets distributed, sleeping spaces covered, person-years of protection, and treated net years.

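### The planned cost per case averted is a gross programme ratio: it leaves out the provider's saving on testing and treatment, so it should be labelled gross and shown beside a net figure

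*Protocol article*

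**What the plan says.** The relevant statements are spread over several sections of the protocol article.

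**Cost side**
- Study objectives: the cost-effectiveness objective uses "data on product prices and costs of delivery and deployment to estimate a mean cost per case averted for each ITN type".
- Cost-effectiveness of dual active ingredient insecticide-treated bed nets: "The costs of each net distribution will be measured from a provider perspective". It adds that "Costs are collected retrospectively for all campaign activities", and the items that follow run from planning and household registration to monitoring and evaluation.
- Costing and cost-effectiveness data analysis: "Total cost is simply total economic cost of the mass distribution of long-lasting insecticide-treated nets over their expected lifetime". The same section describes "economic costs (the value of all resources used during study duration", with no mention of resources saved.

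**Effect side**
- Abstract, Methods: the ICERs are "based on incidence rate ratios calculated from routine data".
- Study objectives: effectiveness is "based upon case incidence rates measured for objective 1".
- Epidemiological surveillance analysis: monthly incidence is obtained by "dividing the number of all positive malaria tests (RDT and blood smear) obtained that month by the estimate health facility catchment area population".
- The passive-surveillance paragraph at the end of the Exclusion section says these data come from outpatient visits or from community health workers.
- The cost-effectiveness section also allows averted cases to come from a transmission model. Treatment seeking enters there as a model parameter, not as a cost.

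**The concern.** Every case in the routine data has, by definition, already used a test in the provider's system, and normally a contact and a treatment as well. When a net averts such a case, some of those resources are released to the provider. The plan counts the case in the denominator but gives no credit for the released resources in the numerator. Three sections state the cost side in positive terms as nets plus distribution, so this is a stated method and not just something a condensed article omits.

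What is at stake is interpretation. The results are meant to guide malaria programmes and donors, and the Background names higher cost and missing cost-effectiveness evidence as obstacles to uptake. A reader who sees a provider perspective and an ICER may take the figure as net of treatment savings. If it is gross, a net that pays for part or all of its extra cost will look dearer than it is to the health system.

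**Working it through.** The documents report no ICER, net price, incidence rate or case-management cost, so there is no figure of the plan's own to reproduce. The check is algebra, followed by an illustration on assumed inputs.

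**Algebra**
- ΔC = incremental cost of nets and distribution; ΔE = cases averted.
- c = provider cost of testing and treating one case; s = share of c actually avoided per counted case.
- Gross ICER = ΔC / ΔE.
- Net ICER = (ΔC − s·c·ΔE) / ΔE = ΔC / ΔE − s·c.
- Gross minus net = s·c, which is positive whenever any cost is avoided.

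**Illustration (every input is an assumption)**

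Take a population of 100,000, 1.8 persons per net (55,556 nets) and 2 years of follow-up, so that ΔC = 55,556 × extra price per net and ΔE = 100,000 × incidence × 2 × (1 − IRR).

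| Extra price | Incidence per person-year | IRR | ΔC (US$) | ΔE | Gross ICER | Net ICER at c = 1 / 3 / 5, s = 1 |
|---|---|---|---|---|---|---|
| US$1 | 0.3 | 0.85 | 55,556 | 9,000 | 6.17 | 5.17 / 3.17 / 1.17 |
| US$1 | 0.5 | 0.70 | 55,556 | 30,000 | 1.85 | 0.85 / −1.15 / −3.15 |
| US$2 | 0.1 | 0.95 | 111,111 | 1,000 | 111.11 | 110.11 / 108.11 / 106.11 |

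The consequence depends on the size of the gross ratio. In the third row even c = US$5 removes only 5 / 111.11 = 4.5%. In the second row the sign changes at c = US$3.

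**Effect of s**

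With c = US$3 the gap is 3 × 0.8 = US$2.40, 3 × 0.6 = US$1.80 or 3 × 0.4 = US$1.20. In the second row at c = US$3, the net ICER is negative only if s exceeds 1.85 / 3 = 0.62.

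**Ranking**

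For two nets A and B compared with the same control, if gross A is below gross B, then gross A − s·c is below gross B − s·c. A common s·c shifts both ratios by the same amount and preserves their order.

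**The case against.** The strongest reply is that the plan is internally consistent. It attaches the provider perspective to the costs of net distribution, names its inputs openly and nowhere promises a net health-system ICER. Gross programme cost per case averted is a recognised measure. This stands: the planned ratio is too high only relative to a net ICER, and it would go too far to say that the plan breaks its own perspective.

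It can also be said that cost offsets are usually left to a health-economic analysis plan. This has some force, but the objective and the definition of total cost do state what goes into the numerator.

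Three stronger inferences are tempting, and the documents do not support them.
- A reader might infer that the gap equals the full unit cost of a treated case. That needs s = 1. Patients may still attend and be tested for another fever. This is plausible where Table 1 shows under-five RDT prevalence of 43.7% to 54.9%, as in Northern Mozambique and Nigeria, because some positive tests may be incidental. Staff costs may also be fixed.
- A reader might infer that every averted case is a facility case. Community health worker cases are included, and modelled cases may never be treated.
- A reader might infer that the omission penalises the more effective net. The total saving left out is larger for that net, but the ratio per case moves by the same s·c for each net in a setting.

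Finally, the literature review that the plan describes is meant to inform uncertainty around measured costs. Case-management cost is not measured, so the review would have to be extended.

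**Conclusion.** The point holds as a matter of labelling and completeness. As written, the plan yields a gross programme cost per case averted, which exceeds a net provider ICER by s·c. The direction is certain for any positive avoided cost. The size is unknown, because the documents contain no unit costs and every dollar figure, incidence and rate ratio in the illustration is assumed.

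For a constant s·c the ordering of net types within a setting does not change. A comparison with a cost-effectiveness threshold, or a conclusion that a net is cost-saving, can change, mainly where the gross ratio is only a few dollars per case. The documents set no threshold, so no planned decision rule is shown to fail. This is a cheap improvement, not an error that undermines the analysis.

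**What to change.** 1. Label the planned ratio as gross programme cost per case averted wherever it is reported.
2. Beside it, report an ICER net of averted case-management cost for each net type and setting: (ΔC − s·c·ΔE) / ΔE.
3. Take c and s from published literature by a small extension of the planned review, separately for facility and community health worker cases where possible. Where modelled cases are used, let s reflect the share that would have been treated.
4. Vary c and s in the probabilistic sensitivity analysis.

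The cost is a modest addition to the literature search in four countries, two more parameters and one more column per ICER table. The downside is that the study measures neither c nor s, so the net figure should supplement the gross one and not replace it.

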### Sampling considerations

#### Epidemiological power

The primary epidemiological outcome for which the evaluations are powered is malaria infection prevalence at the district level, as determined by RDTs in children aged 6 months to 5 years and in Rwanda all ages, assessed during annual community cross-sectional surveys. Within each study district, participants were targeted using a clustered sampling approach, clustering observations at a subdistrict level either by sector, health facility catchment, or village—whichever is most practical. Sample size calculations aim at 80% power to detect either a 30% (Burkina Faso and Rwanda) or a 15% (Mozambique and Nigeria) relative reduction in prevalence in an intervention district compared to a 5% reduction in prevalence observed in the standard pyrethroid-only ITN control district [10].

Sample sizes were estimated in PASS 15.0 (NCSS, LLC; Kaysville, Utah) using the following assumptions:Minimum of 15 households sampled per village.An average relative reduction in prevalence of 5% in the standard pyrethroid-only ITN study district.An average relative reduction in prevalence of 30% (Burkina Faso and Rwanda) or 15% (Mozambique and Nigeria) across the 2-year follow-up.Higher than normal estimates of within-cluster standard deviation (0.3) and within-pair variability (CVM = 0.66) to accommodate the likelihood of higher-than-normal homogeneity within non-randomized ‘clusters’.A one-way test with Power = 0.80 and Alpha = 0.0125 (lower than normal to accommodate Bonferroni’s correction for multiple comparisons of the same control district to the different intervention districts).

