## Methods

### Study sites

The study is composed of five distinct evaluations across four countries, one each in Burkina Faso, Nigeria, and Rwanda and two in Mozambique (Table 1). In each evaluation setting, these observational pilot studies accompany the national malaria control programme (NMCP)-led mass distribution campaigns of 2019 and 2020.

**Table 1 Tab1:** Study districts, type of insecticide-treated bed nets distributed through the mass campaign, and the pre-study baseline prevalence

Country	Study area	ITN AI	ITN brand	Under 5 baseline prevalence* (%)	Primary vector species	Pyrethroid resistance status (WHO tube test mortality)
Burkina Faso [17]	Banfora	Chlorfenapyr + alpha-cypermethrin	Interceptor G2	RDT: 13.8	*An. gambiae*	High (< 50%)
	Gaoua^†^	Standard pyrethroid-only	DuraNet LN, Interceptor, MAGNet, PermaNet 2.0	RDT: 32.4	*An. gambiae*	High (< 50%)
	Orodara	PBO	PermaNet 3.0	RDT: 13.6	*An. gambiae*	High (< 50%)
Northern Mozambique [18]	Mandimba	Pyriproxyfen + alpha-cypermethrin	Royal Guard	RDT: 48.6	*An. funestus*	Moderate (85–100%)
	Cuamba	Chlorfenapyr + alpha-cypermethrin	Interceptor G2	RDT: 48.6	*An. funestus*	Moderate (85–100%)
	Gurue^†^	Standard pyrethroid-only	DuraNet LN	RDT: 44.3	*An. funestus*	Moderate (85–100%)
Western Mozambique [18]	Changara	PBO	Olyset Plus	RDT: 29.4	*An. gambiae*	High (60–85%)
	Guro	Chlorfenapyr + alpha-cypermethrin	Interceptor G2	RDT: 47.6	*An. gambiae*	High (60–85%)
	Chemba^†^	Standard pyrethroid-only	DuraNet LN	RDT: 29.4	*An. gambiae*	High (60–85%)
Nigeria [19]	Asa	Chlorfenapyr + alpha-cypermethrin	Interceptor G2	RDT: 43.7	*An. gambiae*	Variable (12–94%)
	Moro	Pyriproxyfen + alpha-cypermethrin	Royal Guard	RDT: 43.7	*An. gambiae*	Variable (12–94%)
	Ejigbo^†^	Standard pyrethroid-only	DuraNet LN	RDT: 54.9	*An. gambiae*	Variable (12–94%)
	Ife North	Alpha-cypermethrin + PBO	Veeralin	RDT: 54.9%	*An. gambiae*	Variable (12–94%)
Rwanda [20]	Karongi	Chlorfenapyr + alpha-cypermethrin	Interceptor G2	RDT: 3.1 Microscopy: 1.8	*An. funestus*	Low (85–100%)
	Nyamagabe^†^	Deltamethrin	Yahe LN	RDT: 14.4 Microscopy: 8.7	*An. funestus*	Low (85–100%)
	Ruhango	Deltamethrin (and IRS)	Yahe LN	RDT: 14.4 Microscopy: 8.7	*An. funestus*	Low (85–100%)

*IG2* Interceptor G2, *IRS* indoor residual spraying, *ITN* insecticide-treated bed net, *PBO* piperonyl butoxide, *RDT* rapid diagnostic test, *RG* Royal Guard

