*Prevalence surveys were not conducted at the study area level. Details on each survey methodology can be found in the referenced document for each country. Additional details on each evaluation context are available in Additional file 2: Annex S1

^†^Indicates study control area

IG2s were deployed in five districts (Burkina Faso, Nigeria, western and northern Mozambique, Rwanda), RGs deployed in two districts (Northern Mozambique and Nigeria) and PBOs deployed in three districts (Burkina Faso, Western Mozambique, and Nigeria). In Rwanda, one district deployed IRS in combination with standard pyrethroid-only ITNs in comparison to pyrethroid-only ITNs alone (Figs. 1, 2, 3 and 4).

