#### Epidemiological surveillance analysis

The trials are planned under a superiority, difference-in-differences (DiD) framework. The comparisons will consist of one-sided tests of the null hypothesis that the outcomes (reductions in parasite prevalence or case incidence rate from baseline to end line) in each intervention district are statistically the same as the outcomes in the appropriate control district control arm.

Malaria infection prevalence, determined by RDT tests during the cross-sectional surveys, will be analysed by an appropriate difference-in-differences model comparing changes in prevalence from year to year across study districts (intervention type). Considering sample size constraints, a single indicator age group will be targeted using a clustered sampling approach, clustering observations at a sub-district level (either by sector, health facility catchment, or village—whichever is most practical). Statistical analysis is done using Stata (version 14.2 or later). A difference-in-differences approach will assess matched-pair comparisons of the mean change in malaria prevalence from year to year, before and after ITN distribution across each study districts (intervention/control) comparison. The approach taken within each evaluation setting is powered independently to compare changes in prevalence observed in the ITN intervention districts to changes in the prevalence observed in the appropriate ITN control district. However, given the proposed study design and sampling frame, secondary post-hoc analyses, with Bonferroni’s correction for multiple comparisons, will likely be able to detect an effect size difference of around 20% between any two ITN types at 24 months. The protective efficacy of dual-AI ITNs is determined by multilevel logistic regression model for each year, adjusted for age and individual ITN use the previous night, with clustering at the district level.

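### The common one-sided alpha of 0.0125 cannot be the Bonferroni level for every evaluation, because the comparisons per control range from one or two to three and no family-wise level is stated

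*Protocol article*

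**What the plan says.** Under Sampling considerations, Epidemiological power, the sample-size assumptions include "A one-way test with Power = 0.80 and Alpha = 0.0125". The reason given is that the level is "lower than normal to accommodate Bonferroni’s correction for multiple comparisons of the same control district to the different intervention districts". The same figure serves all settings; only the assumed effect differs by country. The article gives neither the family-wise level nor the divisor.

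The section Epidemiological surveillance analysis confirms the sidedness ("The comparisons will consist of one-sided tests of the null hypothesis") and the unit within which comparisons are made: "The approach taken within each evaluation setting is powered independently to compare changes in prevalence observed in the ITN intervention districts". It mentions Bonferroni only for secondary post-hoc comparisons between net types, which are separate from the comparisons with control.

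The number of comparisons follows from the design, which the section on study sites sets out as follows: "The study is composed of five distinct evaluations across four countries, one each in Burkina Faso, Nigeria, and Rwanda and two in Mozambique". One control district is marked in each evaluation (Table 1). On the products, the article says that "IG2s were deployed in five districts (Burkina Faso, Nigeria, western and northern Mozambique, Rwanda"). Royal Guard went to fewer settings: "RGs deployed in two districts (Northern Mozambique and Nigeria"). Nets with piperonyl butoxide (PBO) went to one district each in Burkina Faso, western Mozambique and Nigeria. Table 2 agrees, listing three net types for Nigeria.

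**The concern.** Bonferroni divides a family-wise level by the number of comparisons in the family. The article defines the family as "multiple comparisons of the same control district to the different intervention districts", so the divisor should follow the number of intervention districts per control. That number varies between evaluations but the alpha does not. The stated level and the stated reason therefore cannot agree in every evaluation.

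Prevalence is the outcome on which the evaluations are powered. Nigeria is the only setting that compares all three newer net types (Interceptor G2, Royal Guard and PBO) with one control. If the analysis takes its threshold from the same correction, a one-sided p-value in Nigeria between 0.0083 and 0.0125 would count as significant or not depending on a base that is not written down. The 80% power claim depends on the same unstated choice.

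**Working it through.** **Step 1: comparisons per control (k), from Tables 1 and 2.**
- Burkina Faso: Interceptor G2 and PBO against Gaoua, k = 2.
- Northern Mozambique: Interceptor G2 and Royal Guard against Gurue, k = 2.
- Western Mozambique: Interceptor G2 and PBO against Chemba, k = 2.
- Nigeria: Interceptor G2, Royal Guard and PBO against Ejigbo, k = 3.
- Rwanda: Interceptor G2 against Nyamagabe, k = 1. If Ruhango (standard nets plus indoor spraying) is also compared with Nyamagabe, k = 2.

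**Step 2: reproduce 0.0125.** With alpha = family-wise level / k, family-wise levels of 0.025, 0.05 and 0.10 and k = 1, 2, 3, 4 and 6 were tried. Two combinations give 0.0125 exactly: 0.025/2 and 0.05/4. The first fits the two-comparison settings but not Nigeria. The second fits no evaluation.

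**Step 3: family-wise error when each test uses 0.0125.**
- k = 2: bound 2 × 0.0125 = 0.025; 0.023 with correlation 0.5 between the test statistics.
- k = 3: bound 3 × 0.0125 = 0.0375; 0.0370 if the tests were independent; 0.033 with correlation 0.5.

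Correlation 0.5 is an assumption. It is what a shared control produces when the district-level changes are estimated with equal precision.

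**Step 4: power at the level each base implies.** Take a design with exactly 80% power at one-sided 0.0125. Its standardised effect is 2.241 + 0.842 = 3.083. Power at another alpha is Φ(3.083 − z), where z is the 1 − alpha normal quantile. The sample-size ratio for 80% power is [(z + 0.842)/3.083]².

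| Base and k | Alpha | z | Power | Size ratio for 80% |
|---|---|---|---|---|
| 0.025, k = 3 (Nigeria) | 0.0083 | 2.394 | 75.5% | 1.10 |
| 0.025, k = 2 | 0.0125 | 2.241 | 80.0% | 1.00 |
| 0.025, k = 1 (Rwanda, if one) | 0.025 | 1.960 | 86.9% | 0.83 |
| 0.05, k = 3 (Nigeria) | 0.0167 | 2.128 | 83.0% | 0.93 |
| 0.05, k = 2 | 0.025 | 1.960 | 86.9% | 0.83 |
| 0.05, k = 1 (Rwanda, if one) | 0.05 | 1.645 | 92.5% | 0.65 |

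**Step 5: Nigeria in households.** Table 3 gives 1680 per year. Split equally over four areas (an assumption), that is 420 per area. At 0.0083, 80% power needs 420 × 1.1014, rounded up to 463. At 0.0167 it needs 420 × 0.9278, rounded up to 390.

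The survey sizes cannot show which base was meant, because the article does not give the planning baseline prevalence or the PASS procedure.

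**The case against.** A reader might infer that Nigeria's error rate is inflated. That holds only if the family-wise level is one-sided 0.025, and the article states no such level. On a one-sided 0.05 base, Nigeria's bound of 0.0375 stays below the family-wise level. A divisor larger than the true count is also valid: Bonferroni is an upper bound, so one conservative alpha across evaluations controls error and costs only efficiency. This stands, and under-correction in Nigeria is therefore put here as conditional.

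A reader might also infer that 0.0125 is needlessly strict for Rwanda. The count there is open. Study sites describes the sprayed district as compared with pyrethroid-only nets alone, which gives two comparisons. Study design groups standard nets plus spraying with the controls. With two comparisons and a 0.025 base, 0.0125 fits Rwanda exactly.

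Lastly, 0.0125 is printed as a planning input. The analysis section sets no significance level for the comparisons with control, and a plan that is not shown may do so. It would therefore go too far to call the decision threshold wrong.

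These points do not remove the mismatch. The article prints one level with one reason, and its own tables give counts that the level cannot serve together. A deliberately conservative common divisor would be acceptable, but the article describes the correction by the comparisons sharing a control and mentions no such choice.

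**Conclusion.** The concern holds in this form: 0.0125 and the Bonferroni reason given for it disagree in at least one evaluation on either base that reproduces the figure. Which base applies decides only the direction.

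- **One-sided 0.025:** Nigeria is under-corrected, and its power at the matching level is about 4.5 percentage points below the planned 80%.
- **One-sided 0.05:** every evaluation is planned at a stricter level than its count requires. Nigeria would have about 83% power and the two-comparison settings about 87%.

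The power figures assume exactly 80% power at 0.0125 and a normal approximation. The article says only that its calculations aim at 80%. The effect is moderate and cheap to put right.

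**What to change.** State the one-sided family-wise level. For each evaluation, list the comparisons with control that form the family, and say whether Rwanda's sprayed district counts. Derive each alpha as the family-wise level divided by that count, and restate power at it, notably for Nigeria. If one conservative alpha is wanted throughout, say so and give its divisor.

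In the analysis, apply Holm within each evaluation. It controls the same family-wise error and is never less powerful than Bonferroni, so power restated at the Bonferroni level is a lower bound for each comparison.

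The cost is wording and one recalculation, with no change to data collection. The downside is that Nigeria's stated power may become slightly less favourable, depending on the level chosen.
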